## Abstract

**Background:**

The majority of patients undergoing hepatectomy for hepatocellular carcinoma (HCC) suffer from underlying liver disease and are exposed to the risk of postoperative ascites, which is favored by an imbalance between portal venous inflow and a diminished hepatic volume. Finding a reversible, non-invasive method for modulating the portal inflow would be of interest as it could be used temporarily during the early postoperative course. Somatostatin, a well-known drug already used in several indications, may limit the risk of postoperative ascites and liver failure by decreasing portal pressure after hepatectomy for HCC in patients with underlying liver disease. We aimed to evaluate the impact of somatostatin postoperative infusion on the incidence of ascites following hepatectomy by laparotomy for HCC in patients with underlying liver disease.

**Methods/design:**

The SOMAPROTECT study is a multicenter randomized double-blind placebo controlled phase III trial comparing two arms of patients with underlying liver disease undergoing hepatectomy for HCC by open approach. All patients will have primary abdominal drainage before closure. Patients in the experimental arm will receive a postoperative intravenous infusion of somatostatin during 6 days. Patients in the control group will receive a placebo infusion for the same duration. The primary endpoint will be the presence or absence of postoperative ascites occurring during the 90-day postoperative course, defined as ≥500 ml/24 h of fluid in the drains during at least 3 days or any ascites requiring an invasive procedure comprising percutaneous puncture or drainage. Secondary endpoints will be duration and total volume of ascites, postoperative 90-day mortality and morbidity, liver failure, acute renal failure, length of stay in intensive care unit and hospital stay. The total number of patients to be enrolled was calculated to be 152.

**Discussion:**

Postoperative ascites remains a major issue after hepatectomy for HCC as it is associated with increased morbidity, liver and renal failure, the need for specific treatments and prolonged hospital stay. This study represents the first randomized controlled trial to assess the benefits of somatostatin on the risk of postoperative ascites after surgery for HCC.

**Trial registration:**

NCT02799212 (ClinicalTrials.gov identifier). Registered prior to conducting the research on 9 June 2016.

## Background

Liver resections represent the best therapeutic option for resectable hepatocellular carcinomas (HCCs) in patients not eligible for liver transplantation and also as first-line treatment in some patients with a project for liver transplantation according to the French national policy of organ allocation [1], with a 50–70% 5-year overall survival [2]. The vast majority of patients developing HCC suffer from underlying liver disease, and despite the progress made in terms of perioperative management, patients undergoing hepatectomy for HCC are exposed to the risk of postoperative ascites and subsequent morbidity, which occurs in up to 56% of patients [3]. While the laparoscopic approach may decrease the rate of postoperative ascites after hepatectomy [4], a large proportion of liver resections for HCC are still made through a traditional open approach and therefore, postoperative ascites remains a major concern in that situation.

Postoperative ascites in patients undergoing hepatectomy is associated with an increased risk of overall postoperative morbidity and acute renal failure, the need for specific treatment (including albumin infusion, diuretics and abdominal puncture) and prolonged hospital stay [3]. It is favored by an imbalance between the portal venous inflow and the diminished hepatic venous outflow in the remnant liver, which may lead to portal hyperperfusion, acute portal hypertension and ascites [5]. This phenomenon is known as the small-for-size syndrome, which has been initially described after partial liver transplantation [6] but is also one of the main mechanisms involved in postoperative ascites after hepatectomy [5, 7, 8]. This risk is increased especially in patients undergoing hepatectomy for HCC, as the majority of patients with HCC suffer from underlying liver disease and subsequently, from low or mild portal hypertension.

In order to limit the risk of postoperative acute portal hypertension and ascites, surgical techniques of portal inflow modulation, such as splenic artery ligation, splenectomy and porto-systemic shunts have been proposed after partial liver transplantation [9], and also after extended liver resection in experimental animal models [10–12] and in patients with cirrhosis [13–15]. These techniques aim to divert the portal inflow and decrease portal pressure in order to avoid the small-for-size syndrome and postoperative ascites. However, these surgical methods of portal inflow modulation are invasive and may induce specific morbidity such as hemorrhage, portal thrombosis, asplenia and encephalopathy [16]. Additionally, all reported surgical techniques of portal inflow modulation are irreversible, while liver regeneration mainly concerns the 5 to 7 first days following resection [17, 18]. After that regeneration period, there is no more need for a decrease in portal flow, which might even induce encephalopathy or impair liver regeneration [19]. In this context, finding a reversible and non-invasive method for modulating the portal inflow would be of great interest, as it could be used temporarily during the early postoperative course to limit the risk of acute portal hypertension without having the drawbacks of a definitive and invasive surgical method of portal inflow modulation.

Somatostatin, a natural hormone with splanchnic vasoconstriction properties, is a valid therapy of upper gastro-intestinal bleeding as it decreases both portal flow and pressure in cirrhotic patients [20]. To date, there has been no study assessing the impact of somatostatin infusion on postoperative ascites following partial hepatectomy. However, a few experimental studies have demonstrated the efficacy of somatotsatin in improving the outcome of animals undergoing partial liver transplantation: For instance, Xu et al. demonstrated that somatostatin infusion decreased the portal pressure significantly in a rat model of partial liver transplantation [21]. Hessheimer et al. showed in a porcine model of partial liver transplantation that somatostatin infusion decreased the rate of postoperative ascites and improved the outcome of swine undergoing partial liver transplantation, not only by diminishing the portal pressure, but also by a direct cytoprotective mechanism [22]. In the clinical setting, Ozden et al. reported a single clinical case of post liver transplant small-for-size syndrome successfully treated by somatostatin infusion combined with beta blockers, after failure of splenic artery ligation [23]. Recently, our team assessed the intraoperative effects of somatostatin on splanchnic hemodynamics of swine and showed that somatostatin decreased portal flow and restored a normal hepatic venous pressure gradient in animals undergoing extended hepatectomy [24]. These findings together with somatostatin’s inherent properties suggest that this molecule may play a favorable role in the postoperative course of patients with underlying liver disease undergoing hepatectomy for HCC by open approach.

Therefore, we aimed to test through a multicenter randomized controlled trial the hypothesis that somatostatin infusion after hepatectomy by laparotomy for HCC would decrease the incidence of postoperative ascites.

## Methods/design

### Protocol overview

The SOMAPROTECT study will consist of a multicenter randomized double-blind placebo controlled phase III trial comparing two groups of patients with underlying liver disease undergoing hepatectomy for HCC by open approach, who will receive postoperative infusion of somatostatin or placebo (Fig. 1). After therapy validation in a HCC dedicated oncological multidisciplinary team meeting, patients with a resectable HCC and with underlying liver disease who are eligible for a liver resection by open approach will be considered for inclusion in the study.

**Fig. 1 Fig1:**
[figure not shown]
Study flow chart

In both arms of the study, patients will undergo a hepatectomy by open approach, with intraoperative measurement of portal vein and inferior vena cava pressures before and after liver resection. All patients will benefit from an abdominal drainage. Randomization will be performed after the abdomen is opened and any contraindication for resection (i.e. peritoneal carcinomatosis) has been precluded. Patients will be randomized in equal proportions in two groups. Patients in the experimental group will receive an intravenous postoperative infusion of somatostatin (Eumedica SA, Manage, Belgium) during 5 days at 6 mg/day, followed by one day at 3 mg/day. Treatment will be stopped at the end of day 6. Patients in the control group will receive a placebo infusion consisting of a daily 50 ml intravenous infusion of 0.9% NaCl during 6 days. No additional postoperative infusion or injection of somatostatin or any analogue of somatostatin will be performed during postoperative course.

In order to allow a double-blind design, preparation of somatostatin or placebo will be performed outside the ward where the patient is located by a pharmacist aware of the randomization results. The surgeons and nurses in charge will thus be unaware of the allocated treatment. Intraoperative management of vascular fluids and postoperative management of ascites will be defined by a common protocol. Abdominal drains will be left in place during at least 4 days and will be mobilized systematically from postoperative day 5 onwards.

### Inclusion criteria

The study will include patients with HCC who are eligible for open hepatic resection. The inclusion criteria are as follows: patient age ≥ 18 years; patients with HCC diagnosed by histology or by imaging findings according to the definition of Barcelona Clinic Liver Cancer Group [25]; patients with a single or multiple HCCs deemed to be resectable with a curative intent at the preoperative evaluation; patients for whom an indication for hepatectomy by open approach (laparotomy) has been decided and approved by a multidisciplinary team meeting; patients with any underlying liver disease with or without proven cirrhosis, regarding histological features (including F3-F4 fibrosis with or without cirrhosis) or with other evidence of a diseased liver if no biopsy has been performed preoperatively (dysmorphic liver or evidence of portal hypertension at imaging findings, oesophageal varices at endoscopy); patients with ability to understand and sign a written informed consent form; patients who will be available for follow-up.

### Exclusion criteria

All patients who do not meet all the inclusion criteria will not be included. The other non-inclusion criteria are the common contraindications for surgery related to patient status, disease extension and operative technique. Patient-associated non-inclusion criteria will include: Patients with any other simultaneous experimental treatment and those with evidence of a healthy liver at biopsy (i.e. F0, F1 or F2). Disease-associated non-inclusion criteria will include: another histologic type of hepatic tumor besides HCC; presence of distant extra-hepatic metastases, including peritoneal carcinomatosis; existence of complete portal thrombosis of the main portal trunk. Patients with an indication for laparoscopic approach will also be excluded.

### Endpoints and outcome measurements

The primary endpoint will be the presence or absence of postoperative ascites occurring during the postoperative course (within 90 postoperative days). Postoperative ascites will be defined by the existence of ≥500 ml / 24 h of fluid in the drains during at least 3 days, or any ascites requiring an invasive procedure comprising percutaneous puncture or drainage (radiologically or surgically). This definition of ascites of ≥500 ml/24 h is the most common definition of postoperative ascites in the medical literature: several widely reported studies have used that definition [26–31]. Moreover, Azoulay et al. added to this definition the necessity of a 3-day period, which avoids selection bias related to postoperative fluid caused by bleeding, residual lavage or bile leakage [27]. In addition to this definition, we added the need for an invasive procedure as a definition of ascites because some patients may develop ascites after drain removal, or may develop some ascites that is not drained appropriately by the surgical drain, which will require additional invasive management such as puncture or drainage.

Secondary endpoints are duration and total amount of ascites, postoperative overall 90-day morbidity, the existence and the severity of postoperative liver failure, the existence and the severity of postoperative acute renal failure, postoperative mortality (overall and liver-related), length of stay in intensive care unit, and length of hospital stay. A standardized definition and/or grading system will be considered for all these secondary endpoints as follows: duration of ascites will be defined as the number of days with ascites ≥500 ml/24 h; total amount of ascites will be defined as the total quantity of ascites collected by the drains from surgery to drain removal, associated with the total quantity of ascites collected by radiological puncture or drains if secondary drainage or puncture has been performed; postoperative morbidity will be graded according to the Dindo-Clavien scale [32]; postoperative liver failure will be defined and graded according to the International Study Group of Liver Surgery (ISGLS) definition and grading system [33]; postoperative acute renal failure will be defined according to the “Acute Dialysis Quality Initiative” (ADQI) definition and graded according to the “Risk, Injury, Failure, Loss, End-stage kidney disease” (RIFLE) Scale [34]; postoperative mortality will be defined as any death occurring within 90 postoperative days. Cases of death will be divided into liver failure-related versus liver failure-unrelated deaths.

### Randomization

Patients will be randomized during the operative procedure after the abdomen has been opened and the peritoneal cavity explored, precluding any contraindication for surgical resection. For patients in the experimental arm, an intravenous infusion of somatostatin (Eumedica SA, Manage, Belgium) at full-dose (6 mg/24 h) will be started at abdominal closure, and performed during 5 days, followed by a half-dose (3 mg/24 h) infusion during 1 day before it is stopped. Patients in the control arm will receive placebo infusion consisting of 50 ml intravenous infusion of 0.9% NaCl during 6 days.

The randomization will be performed using the stratified block randomization method for each center. A randomization list will be generated for each center and envelopes will be prepared and blinded for allocation during surgery according to consecutive inclusion.

### Preoperative work-up

Patients eligible for study will undergo complete conventional preoperative work-up, including physical examination, standard blood test (comprising hemostasis tests, platelet count, indocyanin green clearance test, dosage of liver enzymes, alpha-fetoprotein, serum creatinine concentration), oesogastroscopy for evaluation of oesophageal and/or gastric varices, thoraco-abdomino-pelvic computed tomography (CT), to assess resectability and search for extrahepatic metastasis, portal thrombosis, other signs of portal hypertension (venous collaterals, splenomegaly), tumor features will be precisely evaluated by radiologists regarding size, number, the Milan Criteria [35] and the Alpha score [36]. Evaluation of the cardiac function is optional and left at the anesthesiologist’s discretion regarding patient background. All patient files will be discussed at a multidisciplinary staff, and the indication for hepatectomy by open approach will be validated before any consideration for patient inclusion.

### Treatment methods

#### Global preoperative care

Administration of immunonutrition (Oral Impact®, Nestlé) will be performed in all patients 7 days before surgery. Cessation of alcohol drinking will be requested at least one month before surgery.

### Anaesthetic technique

Premedication will be administered at the team’s discretion. Patients will receive prophylactic antibiotics 30 min prior to the abdominal incision. Standard monitoring will be performed using 2 peripheral venous catheters, while the placement of a central venous catheter and/or an arterial pressure monitoring catheter is not mandatory and left at the anesthesiologist’s discretion. No epidural analgesia will be used as patients with underlying liver disease may exhibit hemostatic disorders, thus increasing the risk of epidural bleedings.

Induction of general anesthesia will be performed with intravenous injection of propofol, remifentanil, and Cis-astracurium. Maintenance of general anesthesia will be performed with halogen gas, remifentanil and myorelaxation will be obtained with intravenous boluses of cis-astracurium. Ventilation will be performed with a 6 to 8 ml/kg tidal volume, a positive end-expiratory pressure around 5 cmH_2_O, and the respiration frequency will be adjusted to maintain end-tidal CO^2^ between 30 and 35 mmHg. Regarding the intraoperative conditions, the positive end-expiratory pressure could be modified or even interrupted at anesthesiologist’s discretion.

Administration of intravenous fluids will be performed appropriately regarding the cardio-circulatory monitoring with a regimen of 4 to 6 ml/kg/h of isotonic crystalloid solution, at the anesthesiologist’s discretion. Packed red blood cell transfusion will be performed in case of blood loss > 1500 ml or anemia < 7 g/dl (or < 10 g/dl in case of coronary disease). No prophylactic antifibrinolytic agent will be used systematically.

### Surgical technique

All procedures will be performed by open approach, and will begin with a careful exploration of the abdominal cavity to preclude any contraindication for resection. The type of incision, the parenchymal transection technique, and the choice of portal clamping will be left at the surgeon’s discretion.

### Intraoperative measurement of hepatic venous pressure gradient

An intraoperative measurement of the hepatic venous pressure gradient will be performed after hepatectomy and after hemodynamic stability is obtained. A direct puncture of the portal vein followed by direct puncture of the infra hepatic inferior vena cava will be performed, using a 0.5 mm trocar connected to an arterial pressure monitoring catheter, which itself will be connected to a cardio-tensional scope, thus displaying the pressure value. The hepatic venous pressure gradient will be calculated with the following formula (*Hepatic venous pressure gradient = Portal venous pressure – infrahepatic inferior vena cava pressure*).

### End of the surgical procedure

At the end of each procedure, a surgical drain will be placed within the surgical site in order to drain the abdominal cavity and potential postoperative fluids. The modality of drainage utilized will be standardized in each center and will consist of the use of a closed-circuit drain without suction.

### Somatostatin or placebo administration

The treatment is started after abdominal closure and stopped after 6 days in both arms. No postoperative administration of somatostatin or any somatostatin analog will be performed postoperatively. The administration of placebo will not induce any significant changes in the management of patients, given all patients undergoing hepatectomy have intravenous treatments during this period.

### Postoperative care

#### Global postoperative care

After hepatectomy, the patient will stay in an intensive care unit during a short period of 2 to 4 days (for information purposes only, the duration is left at the discretion of the team in charge of the patient) or will return directly to the conventional hospitalization unit. Besides the postoperative infusion of somatostatin (experimental arm) or placebo (control arm), all other postoperative therapies will be standardized for all patients regardless of the arm in which patients are included. In addition, patients will benefit from a standard postoperative monitoring including physical examination (including umbilical circumference, weight, heart rate, arterial pressure, urine out-put) twice a day, standard liver tests and renal blood tests at postoperative day 1, then every 48 h until postoperative day 15 (postoperative days 3, 5, 7, 9, 11, 13, 15) or patient discharge. The tested blood parameters must include: INR, prothrombin time, serum total bilirubin, SGOT, SGPT, and creatinine. Other blood tests may be performed at the physician’s discretion. The glomerular filtration rate will be estimated according to the CKD-EPI formula. A computed tomography will be performed approximately one month after the procedure (+/− 5 days), to assess the presence of subclinical ascites or other intra-abdominal cavity complications.

### Abdominal drain

All patients will benefit from the placement of a surgical drain during the operative procedure. All drains will be left in place during 4 days without any mobilization. Drain mobilization will start at postoperative day 5. The total amount of fluid in the drains will be monitored every 8 h until drain removal.

### Management of postoperative ascites

The management of postoperative ascites will be standardized according to the International Ascites Club’s recommendations [37] and will be the same for all patients in each participating center No systematic fluid restriction will be performed. Water drinking will be allowed at postoperative day 1, while oral feeding will be authorized once bowel activity has returned. Administration of 1 l/day of intravenous fluids will be performed until day 2, then stopped. The type of fluid administered will be crystalloid isotonic solution. In case of postoperative ascites development, the standardized treatment will associate:Water restriction (1 l/day) and salt restriction20% albumin: 200 ml per day + 100 ml for every 3 l of drained ascitesAdministration of diuretics:Spironolactone, starting at 50 mg/day; increased from 25 mg every 48 h in the absence of any decrease in ascites, with a maximum dosage of 200 mgIn the absence of acute renal failure, furosemide will be associated to spironolactone at a dosage of 20 mg/day, increased to 40 mg/day after 48 h in the absence of any decrease in ascitesDiuretics will be administered orally or intravenously in case of intestinal ileus.

This specific treatment of ascites will be discontinued 48 h after ascites resolution.

In case of evidence of intraabdominal infection or tense ascites as defined by the International Ascites Club [37], an invasive procedure will be performed to evacuate the intraabdominal fluid. The choice between puncture, radiological or surgical drainage is left at the physician’s discretion. In all other clinical situations, invasive procedures will be avoided in first intent.

### Management of postoperative acute renal failure

A major attention will be paid to depict acute renal failure during the postoperative course, as it is associated with a significant increase in postoperative morbidity, ranging from 5 to 15% [38]. In case of acute renal failure, a stage-specific treatment will be performed based on the RIFLE (Risk, Injury, Failure, Loss, End-stage) scale, as follows:*In case of “risk” of acute renal failure (R, increase of creatinine by a ratio of 1.5, or 25% decrease of glomerular filtration rate, or urine out-put below 0.5 ml/kg/h during 6 h),* the management includes an initial decrease in diuretics dosage (or discontinuation if minimum dosage were used), followed by complete discontinuation if no improvement occurs after 48 h.*In case of “injury” of the kidney (I, increase of creatinine by a ratio of 2, or a 50% decrease of glomerular filtration rate, or urine out-put below 0.5 ml/kg/h during 12 h),* the management includes discontinuation of diuretics, followed by intravenous administration of 1000 ml/day of crystalloid fluids (and albumin [60 g/day] in case of postoperative ascites) if no improvement occurs after 48 h.*In case of “failure” of the kidney (F, increase of creatinine by a ratio of 2, or a 50% decrease of glomerular filtration rate, or urine out-put below 0.5 ml/kg/h during 12 h),* the management includes discontinuation of diuretics combined with intravenous administration of 1000 ml/day of crystalloid fluids (and albumin [60 g/day] in case of postoperative ascites).

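### The renal failure treatment rule prints the same thresholds for RIFLE Injury and Failure but attaches different fluid management to them

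*Protocol article*

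**What the plan says.** All of this is in the protocol article.

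- Management of postoperative acute renal failure opens with the promise that "a stage-specific treatment will be performed based on the RIFLE (Risk, Injury, Failure, Loss, End-stage) scale". Three stages follow, each with criteria and management.
- Risk is given as "R, increase of creatinine by a ratio of 1.5, or 25% decrease of glomerular filtration rate, or urine out-put below 0.5 ml/kg/h during 6 h". Diuretics are reduced, then stopped if there is no improvement after 48 h.
- Injury is given as "I, increase of creatinine by a ratio of 2, or a 50% decrease of glomerular filtration rate", or low urine output over 12 h. Diuretics stop. Crystalloid at 1000 ml/day is then conditional: "and albumin [60 g/day] in case of postoperative ascites) if no improvement occurs after 48 h".
- Failure is given as "F, increase of creatinine by a ratio of 2, or a 50% decrease of glomerular filtration rate", or low urine output over 12 h. The management is "discontinuation of diuretics combined with intravenous administration of 1000 ml/day of crystalloid fluids", with 60 g/day of albumin if there is ascites. There is no waiting period and no condition.
- Management of postoperative ascites sets the background fluid: "Administration of 1 l/day of intravenous fluids will be performed until day 2, then stopped". Once ascites develops, water is restricted to 1 l/day and 200 ml/day of 20% albumin is given, plus 100 ml per 3 l of ascites drained.
- Endpoints and outcome measurements grades renal failure severity by the RIFLE scale through a citation (reference 34) and prints no thresholds of its own.

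**The concern.** A rule that treats by stage needs criteria that separate the stages. Here two stages with different management share one set of criteria, so the printed text cannot tell staff which applies. What differs is whether extra crystalloid starts at once or is held back for 48 h to see whether stopping diuretics is enough. These patients have diseased livers, have just had a hepatectomy, and may be under water restriction for ascites, so an added 1000 ml/day is a real clinical decision. Global postoperative care also says that therapies other than the study drug are standardized for all patients. A rule that two centres can apply differently, each in line with the text, does not achieve that.

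The matter at stake is patient care and consistency of care. It is not the trial's inference.

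**Working it through.** There is no statistical figure to reproduce. The check sets the printed criteria and actions side by side.

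**Step 1: criteria** (Management of postoperative acute renal failure)

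| Criterion | Risk | Injury | Failure |
|---|---|---|---|
| Creatinine ratio | 1.5 | 2 | 2 |
| Fall in glomerular filtration rate | 25% | 50% | 50% |
| Urine output below 0.5 ml/kg/h for | 6 h | 12 h | 12 h |

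Thresholds that change from Risk to Injury: 3 of 3. From Injury to Failure: 0 of 3. A word-for-word comparison of the Injury and Failure criteria after the stage letter found them identical. Any patient who meets one set therefore meets the other.

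**Step 2: actions**

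| | Injury | Failure |
|---|---|---|
| Diuretics | stop | stop |
| Crystalloid in first 48 h | none specified | 1000 ml/day |
| Crystalloid after 48 h, not improving | 1000 ml/day | 1000 ml/day |
| Crystalloid after 48 h, improving | none specified | no condition on improvement stated |

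Over the first two days the specified difference is 2 × 1000 = 2000 ml. Routine intravenous fluid ends after day 2, so from then on this is the difference between some and no protocol-specified intravenous crystalloid.

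**Step 3: what the printed rule then does**

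- If both stages are taken to apply, the same patient is subject to two instructions that disagree for the first 48 h.
- If the highest stage met governs, every patient who meets Injury also meets Failure and is treated as Failure. The Injury tier is never reached and its 48 h wait is never used.

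Under neither reading can the stage-specific 48 h wait be applied as printed.

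**Step 4: albumin**

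In this section albumin is given only if there is ascites. The ascites section already gives such patients 200 ml × 20 g/100 ml = 40 g/day, plus 100 ml × 20 g/100 ml = 20 g for each 3 l drained. The text does not say whether the 60 g/day replaces this or is added to it. If it replaces the 40 g/day base, the step is 60 − 40 = 20 g/day, and nothing on a day when 3 l is drained (40 + 20 = 60). If it is added, the step is 60 g/day. Either way the stage affects a dose step or addition and does not decide whether albumin starts.

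**Step 5: is it resolved elsewhere?**

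No other section prints a separate Failure threshold. The endpoint section names RIFLE and its source but gives no numbers.

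**The case against.** The strongest case on the other side has five parts.

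1. *The stages are nested, so there is no true conflict.* A ratio of 2 also exceeds 1.5, a 50% fall exceeds 25%, and 12 h exceeds 6 h. Risk and Injury also carry different actions without a precedence rule, and nobody finds that pair unclear, because the higher stage is understood to govern. This stands. A reader might infer that the rule is irresolvable; on the highest-stage reading it is not. But that reading makes Injury an empty tier, which is still a defect in a rule meant to be stage-specific.

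2. *Albumin is already running.* This stands in full. A reader might infer that the label decides whether albumin starts. The ascites section does not support that, because the eligible patients are already due 40 g/day and neither stage tells staff to stop it.

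3. *RIFLE is named and cited, so sites can stage from the source.* This is partly right, and it is why the correction is easy. But the section prints its own criteria for use at the bedside. A clinician who substitutes other values is overriding the printed rule, not following it.

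4. *The management lists are not exclusive.* Each says what management includes, so crystalloid in the first 48 h of Injury is not forbidden. This stands: the contrast in Step 2 is between what is specified, not between permitted and prohibited.

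5. *Nothing in the trial's inference is touched.* This also stands. A reader might infer that the renal severity endpoint would be misgraded or the arms treated differently. The endpoint is graded by citation to RIFLE, not by these printed thresholds, and the rule is the same in both arms of a double-blind trial. Misgrading would need sites to grade from this section, and the article does not tell them to.

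**Conclusion.** The point holds as a minor error in a care rule. The Failure thresholds repeat those of Injury (0 of 3 differ) while the management differs in when 1000 ml/day of crystalloid starts and whether it is conditional. The two stages cannot be told apart as printed, so the 48 h wait specified for Injury is either contradicted or never used. For albumin the consequence is limited to the 60 g/day step or addition over an existing 40 g/day.

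No effect is shown on the primary endpoint, sample size, power, between-arm bias or the renal severity endpoint. The article gives no incidence by RIFLE stage, so the number of patients concerned cannot be estimated.

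Two assumptions remain. A copying slip in the Failure line is the likely cause, but the article alone cannot prove it. Whether the operational protocol used at the sites has the same wording cannot be seen either, so it should not be inferred that patients were or will be managed wrongly.

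**What to change.** In Management of postoperative acute renal failure, replace the three Failure thresholds with those of the RIFLE source already cited in Endpoints and outcome measurements (reference 34). The values should be taken from that source directly; the article does not print them, and none are supplied here. Check the operational protocol, and notify sites only if it carries the same wording. Leave the management attached to each stage and the endpoint grading as they are.

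The cost is one corrected parenthesis, one check of the operational protocol and possibly a short site notice. Sample size, visits, data collected and endpoint definitions do not change.
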